### Data management and analysis

#### Data management

All study data will be collected and managed using secure REDCap electronic data capture tools hosted at Charles University, Prague [69]. To further ensure data confidentiality, data access rights to REDCap will be granted to only a few members of the research team and selectively constrained according to their roles in the trial. Patients' Fitbit data will be stored in a pseudonymised form on a secure HealthReact server. Patients' study information will not be released outside of the study without the patient's written permission.

The trial is not overseen by an independent data monitoring committee as it neither recruits vulnerable populations, poses any unusual risk to trial participants, nor assesses mortality or major morbidity outcomes [89, 90]. The trial results will be disseminated in open-access scientific journals regardless of the magnitude or direction of effect, and a completely deidentified dataset will be made openly available in an appropriate data repository.

#### Statistical analysis

The primary outcome (change in daily step count at six months) will be analysed using a linear mixed-effect model accounting for clustering at the GP level (random effect) and adjusted for baseline value, prediabetes/diabetes condition, and sex (fixed effects) [91]. The intervention effect (adjusted value for change in intervention minus change in control) will be reported as the mean (95% CI) and associated *p*-value (considered significant at p < 0.05). The intervention effect for secondary outcomes (Table 1) will be assessed using the same approach and reported as a mean (95% CI). However, individual *p*-values will not be reported for secondary outcomes as the adjustment for multiple testing will not be undertaken, and outcomes will be interpreted with caution in relation to the overall pattern of results. Assumptions of normality will be tested, and an alternative distribution will be used where necessary. Baseline characteristics will be compared between the intervention and control arms. If meaningful differences are demonstrated, the measure will be added to statistical models as a covariate. The analyses of the outcomes will be undertaken using both the intention-to-treat principle, considering all patients as randomised regardless of protocol adherence, and a per-protocol analysis, including only patients (a) syncing their Fitbit trackers at least once a month (both arms), (b) engaging in at least five phone counselling sessions, and (c) receiving text messages for the entire study duration (intervention arm only). The impact of missing data will be assessed using a sensitivity analysis, and missing data will be imputed using multiple imputations created by predictive models based on the patients with complete data [92]. All statistical analyses will be performed using an R environment for statistical computing.

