## Methods

### Trial design

This 12-month pragmatic, multicentre, randomised, controlled trial with two parallel arms consists of two phases, each lasting for six months: the lead-in phase, when the mHealth intervention is supported with human phone counselling, and the maintenance phase, when the mHealth intervention is fully automated, without any human support. The primary outcome, average ambulatory activity (steps/day) measured by a wrist-worn accelerometer Actigraph, will be assessed at the end of the maintenance phase at 12 months. A trial scheme is shown in Fig. 1.

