### Sample size

To detect a difference of 1000 steps/day at 12 months between arms, with a power of 80%, using a 2-sided 0.05 significance level (alpha), and anticipating the standard deviation of 3000 steps/day [21, 40, 46], 143 subjects per arm (286 in total) will be needed. To account for an expected attrition rate of approximately 15% [21, 40, 46], we plan to recruit 340 patients for the trial. The increase of 1000 steps/day is equivalent to about 10 min/day of brisk walking [61] and equates to around a 4% decrease in the risk of cardiovascular morbidity and mortality in individuals at high cardiovascular risk with impaired glucose tolerance [62].

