### Outcome measures

Outcomes will be assessed at baseline and 3, 6, and 12 months after randomisation, as described in Table 1. The primary outcome is defined a priori as the change in average daily step count from baseline to 12 months. All other outcomes and comparisons are defined as secondary outcomes.

Average daily step count and other measures of physical behaviour and sleep will be objectively assessed by accelerometry using Actigraph wGT3X-BT worn on a non-dominant wrist for seven days, 24 h a day. The measures will be derived from raw-accelerometry files using an open-access package GGIR in R according to standard procedures, including detection of non-wear and calculation of the average magnitude of dynamic acceleration corrected for gravity (Euclidean Norm minus 1 g) over 5-s epochs [76, 77]. Non-wear will be imputed using the default setting, and patients will be excluded if their post-calibration error is > 0.01 g (10 mg) or they have < 3 days of valid wear (defined as > 16 h per day), or their wear data are not present for each 15-min period of the 24 h cycle [78]. The other physical behaviour measures will include average acceleration, intensity gradient, and acceleration above which a person’s most active 10, 30, 120 and 480 min are accumulated, time spent sedentary and in sedentary bouts > 30 min, and time spent in light, moderate and vigorous PA [79, 80]. The sleep measures will be calculated using automated sleep detection [81], without using a sleep log, and will include sleep time (accumulated nocturnal sustained inactivity bouts), sleep window (time difference between falling asleep and waking up, including time being awake during the night), sleep onset and wake time, and sleep efficiency (ratio of sleep time compared with sleep window) [82].

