## Conclusions

There is an urgent need for effective, sustainable, and scalable PA interventions for (pre)diabetes patients that can be translated to routine primary care [17, 22]. Based on recent evidence and harnessing the latest technology advances, we have developed an mHealth intervention based on JITAI principles to be introduced to the patients by their GPs with initial lead-in support by trained phone counsellors. The intervention will be tested in the pragmatically designed randomised controlled trial ENERGISED, with the primary outcome being a change in daily step count assessed at 12 months. In addition, we will conduct an extensive process evaluation using mixed methods and Ecological Momentary Assessment to be able to further improve the next iteration of the intervention. If shown to be effective, we will seek to implement the intervention as part of the standard primary care in the Czech Republic for (pre)diabetes patients and potentially other patient populations, potentially leading to important public health benefits.

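### The statistical analysis section places the primary test at six months, although the protocol defines, powers and describes the primary outcome at 12 months

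*Protocol article*

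**What the plan says.** The Statistical analysis section opens with: "The primary outcome (change in daily step count at six months) will be analysed using a linear mixed-effect model". It then attaches a p-value, judged at 0.05, to this outcome. Secondary outcomes get an estimate and confidence interval but no p-value, because no multiplicity adjustment is planned.

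Elsewhere the time point is 12 months:

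- Outcome measures: "The primary outcome is defined a priori as the change in average daily step count from baseline to 12 months", followed by "All other outcomes and comparisons are defined as secondary outcomes".
- Trial design, with the same statement in the abstract: the primary outcome "will be assessed at the end of the maintenance phase at 12 months".
- Sample size: "To detect a difference of 1000 steps/day at 12 months between arms".
- Conclusions: "with the primary outcome being a change in daily step count assessed at 12 months".

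The Discussion also mentions the primary outcome, but without a time point. No section explains why the analysis sentence differs.

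**The concern.** Six months cannot be dismissed as an impossible value. It is a scheduled assessment with the same accelerometer measurement, so an analyst could carry out the sentence exactly as written.

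The two contrasts estimate different things. At six months the intervention arm is at the end of a period of repeated phone counselling, so the contrast measures messages plus human support. At 12 months the patients have had six months of automated messages, with only a closing call after the six-month assessment. That later contrast speaks to whether the effect lasts without human support, which is the trial's stated rationale. The Background stresses effects that fade: in one primary care trial of nurse consultations plus a pedometer, an advantage of about 500 steps/day at three months had gone by 12 months.

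Two things are at stake. Read literally, the one confirmatory p-value would go to the wrong contrast. And because the published text contains support for both time points, a later choice of either would be hard to show as pre-specified.

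**Working it through.** **1. The sections side by side**

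| Section | Time point of the primary outcome or powered difference |
|---|---|
| Abstract | 12 months |
| Trial design | 12 months |
| Sample size | 12 months |
| Outcome measures | 12 months |
| Conclusions | 12 months |
| Statistical analysis | six months |

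Under Outcome measures, the six-month contrast is secondary. Under Statistical analysis, a secondary outcome has no p-value. Yet the same section gives the six-month contrast the only p-value. If its sentence is followed, the 12-month contrast is left without one. The two sections cannot both be applied.

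**2. The plan's own sample size**

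Inputs from the Sample size section: difference 1000 steps/day, SD 3000 steps/day, two-sided alpha 0.05, power 80%, attrition about 15%.

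- Normal approximation: n per arm = 2 × (1.96 + 0.8416)² × (3000/1000)² = 2 × 7.849 × 9 = 141.3, rounded up to 142.
- Two-sample t-test with the same inputs: 142.2, rounded up to 143. This is the stated figure, and 2 × 143 = 286.
- Attrition: 286 / 0.85 = 336.5, rounded up to 337, against 340 planned. Recruiting 340 leaves 340 × 0.85 = 289.

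The figures reproduce, and the section ties them to 12 months. Correcting the analysis sentence therefore alters none of them.

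**3. What an open choice between the two time points would cost (illustration)**

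Assume both contrasts are null, each is tested at two-sided 0.05, and either could be named primary. With test statistics Z6 and Z12 that are bivariate normal with correlation r, the chance of at least one false positive is 1 − P(|Z6| < 1.96 and |Z12| < 1.96). For r = 0 this is 1 − 0.95² = 0.0975.

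| Assumed r | Chance of at least one false positive |
|---|---|
| 0 | 9.75% |
| 0.3 | 9.5% |
| 0.5 | 9.1% |
| 0.7 | 8.3% |
| 0.8 | 7.8% |
| 0.9 | 7.0% |

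The protocol gives no correlation, so r is an assumption. The contradiction in step 1 does not depend on this table.

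**The case against.** The strongest reply is that this is a slip which the document already resolves. Outcome measures gives an explicit a priori definition at 12 months and makes everything else secondary; the analysis section has only a parenthesis that describes an outcome already defined. Four further places agree with the definition. On that view there are not two equal candidates, and the error inflation is hypothetical. Those analysing the data are also to be blinded to allocation.

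Much of this stands:

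- Twelve months is clearly the intention.
- The inflation figures describe what could happen if the choice were left open, not the operating characteristics of the plan as intended. High correlations are plausible for repeated step counts adjusted for the same baseline, so the lower end of the range deserves weight.
- The power calculation offers no separate harm. With the same difference and SD, 143 per arm gives the same power at six months.
- The nurse-and-pedometer trial shows that such effects can fade. As reported in the Background it has no six-month result, so it cannot show that the two answers would differ here.

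What does not stand is the inference that nothing needs doing. The error sits in the operative sentence, the one an analyst implements and a reader checks against the results paper. Analyst blinding does not settle the point, because a two-sided p-value at each time point can be seen without knowing which arm is which. The Blinding section also says that patients and researchers are not blinded.

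**Conclusion.** The concern holds. The sentence that specifies the confirmatory model and its p-value contradicts the protocol's own definition of the primary outcome, and as written it is wrong. Its direct consequence needs no assumption: taken literally, the trial's single test would be made at the end of the counselled phase, and the contrast for which the trial was sized would go untested.

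The possible inflation of the type I error, from 5% to between about 7.0% and 9.5%, is secondary. It rests on an assumed correlation of 0.9 down to 0.3 and on the choice of time point actually being left open. Because the point concerns which test is primary, it must be corrected even though the intended answer is plain.

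**What to change.** In the Statistical analysis section, change the time point in the description of the primary outcome from six months to 12 months, to match Outcome measures. For clarity, add that the step-count contrasts at three and six months are secondary and are reported with confidence intervals but without p-values. This follows from rules the protocol already contains and adds no new one. If a separate analysis plan exists, check that it names the same time point. Date the correction, and make it before anyone looks at outcome data by arm.

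The cost is a one-line correction. The sample size (143 per arm, 286 in total, 340 recruited), the visit schedule and the data collection stay as they are.

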#### Phone counselling

To facilitate the adoption of the mHealth intervention, counsellors recruited from among the university students and trained by the research team members (CW, TV, JK, JN) will contact the patients by phone at the start of the intervention, at months 1, 2, 3, 4 and 5, and after the six-month assessment (i.e., seven phone calls altogether, each lasting approximately 10 to 20 min). In addition to enabling the implementation and tailoring of the mHealth intervention to individual patients, the counsellors will use various behavioural change techniques (Table 2) to support patients in the desired behavioural change and enhance their adherence to the intervention.

During the first phone call, approximately one to two weeks after the second baseline visit to the GP, the counsellor will check the patients’ baseline mean daily step count as recorded by Fitbit during the previous week when the patients were supposed not to change their physical behaviour. The counsellor will initially recommend the patients increase their daily step count by at least 3000 above their baseline gradually over at least six weeks. However, if patients are not comfortable with the increase of 3000 steps, they can suggest a goal that they feel is more realistic. Importantly, the counsellor will make sure that the patients have a goal that they consider their own and not imposed on them by the counsellor [74, 75]. Finally, the daily step goal will be converted to a weekly step goal (multiplying by 7), allowing more flexibility in planning the walks. Furthermore, the patients will be encouraged to think about the opportunities for taking these extra steps and develop their own action plans. If patients have difficulties devising the action plan, the counsellor can suggest potential opportunities for including walking into their daily routine (walking as part of daily commuting, walking after a meal, walking with (grand)children, walking a dog, walking meetings, etc.).

The information collected during the first call will then be used by the counsellor to set and tailor the mHealth intervention. Specifically, the weekly goal will be used to inform the review of the weekly step goal and feedback on weekly performance, and the action plan will be used to set the content and timing of the respective reminders.

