During the next calls (months 1 to 5), the counsellor will support the patients in reviewing their step goals and action plans, address the barriers to achieving their plans, advise them to seek social support, provide them with feedback, and encourage them to increase their walking pace and interrupt their prolonged sitting episodes regularly. During these calls, the counsellor can adjust the mHealth intervention and adapt it to changing patients’ needs. Specifically, if the patients regularly achieve their step goal, the counsellor can challenge them to increase it. The call at five months will be scheduled at least two weeks before the six-month assessment to avoid potential patients’ reactivity that could inflate their PA outcomes at six months.

After the assessment at six months, the counsellor will have a final contact with the patients to encourage them to maintain or further increase their achieved levels of PA and remind them that they will continue receiving text messages for six more months.

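### The primary model clusters on GP only, although several counsellors work in the intervention arm alone; if 12-month outcomes correlate within counsellor, the standard error is too small

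*Protocol article*

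**What the plan says.** **Analysis.** The Statistical analysis section gives the primary model as a "linear mixed-effect model accounting for clustering at the GP level (random effect"), with fixed effects for baseline value, condition and sex. GP is the only clustering term.

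**Who delivers the counselling.** The Phone counselling section describes "counsellors recruited from among the university students and trained by the research team members". There are seven calls of roughly 10 to 20 minutes, from the start of the intervention until just after the six-month assessment. At the first call the step goal is agreed and an action plan is developed, and the counsellor uses both to set up the goal reviews, feedback and reminders. At months 1 to 5, "the counsellor can adjust the mHealth intervention and adapt it to changing" needs. Table 2 and the Intervention arm section place all of this in the intervention arm only, with the text messages running for the full 12 months.

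**Sample size.** The Sample size section states "To detect a difference of 1000 steps/day at 12 months between arms", 80% power, a two-sided 0.05 level and "anticipating the standard deviation of 3000 steps/day", and concludes that "143 subjects per arm (286 in total) will be needed". It mentions neither an ICC nor a design effect.

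**The concern.** Patients are individually randomised, and both arms get the same advice from their own GP. A GP effect is therefore largely shared by the two arms and mostly cancels from the treatment contrast. A counsellor effect does not cancel, because only one arm has counsellors. The design is partially nested: intervention patients are grouped by counsellor and control patients are not grouped at all.

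Counsellors who differ in how they negotiate goals, shape action plans and set up messages could make their own patients' outcomes alike. Any such positive correlation raises the variance of the intervention-arm mean. A GP random intercept would not capture this. Even if counsellors were matched to practices, a GP-by-arm term would be needed. At stake are the interval and the p-value of the primary outcome, which is the only p-value for an intervention effect that the plan intends to report.

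**Working it through.** **Inputs from the Sample size section.** Difference 1000 steps/day, SD 3000, two-sided alpha 0.05, power 80%, 143 evaluable per arm.

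**Assumed inputs, not in the document.** Number of counsellors K = 5, 10 or 20; ICC = 0.01, 0.02 or 0.05; one counsellor per patient; equal caseloads.

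**Step 1: reproduce the plan's figure.** The two-sample t-test formula gives 142.2, that is 143 per arm. With 143 per arm and independent patients, SE = 3000 × √(2/143) = 354.8, and power = Φ(1000/354.8 − 1.96) = 80.5%. The stated figure reproduces with no design effect, so it assumes independence in both arms.

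**Step 2: add counsellor clustering in one arm.**
- Caseload m = 143/K
- Design effect, intervention arm: DE = 1 + (m − 1) × ICC; control arm: 1
- Ratio of true SE to the independence SE: R = √((1 + DE)/2)
- Type I error if clustering is ignored: 2 × (1 − Φ(1.96/R))
- Power on the plan's unadjusted basis: Φ(1000/(354.8 × R) − 1.96)

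For K = 10, m = 14.3. At ICC 0.02, DE = 1 + 13.3 × 0.02 = 1.266, R = √(2.266/2) = 1.064, type I error = 2 × (1 − Φ(1.841)) = 6.6%, and power = Φ(1000/377.6 − 1.96) = 75.4%.

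| Counsellors (m) | ICC | R | Type I error | Power, unadjusted basis |
|---|---|---|---|---|
| 20 (7.2) | 0.01 | 1.015 | 5.4% | 79.3% |
| 20 | 0.02 | 1.030 | 5.7% | 78.1% |
| 20 | 0.05 | 1.074 | 6.8% | 74.7% |
| 10 (14.3) | 0.01 | 1.033 | 5.8% | 77.9% |
| 10 | 0.02 | 1.064 | 6.6% | 75.4% |
| 10 | 0.05 | 1.154 | 9.0% | 68.5% |
| 5 (28.6) | 0.01 | 1.067 | 6.6% | 75.2% |
| 5 | 0.02 | 1.130 | 8.3% | 70.4% |
| 5 | 0.05 | 1.300 | 13.2% | 58.2% |

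These are normal approximations. R is how much larger the true SE is. As a share of the true SE, the shortfall is 1 − 1/R, for example 6.1% at R = 1.064. Type I error here refers to an average effect of zero over counsellors who nevertheless differ.

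**Step 3: is power really below 80%?** The analysis adjusts for baseline, but the sample size mentions no baseline correlation. If 3000 is the SD of the 12-month value (the document does not say whether it is a value or a change) and the baseline correlation is ρ (assumed), the SE is multiplied by √(1 − ρ²). Taking the ICC as that of the adjusted outcome, 10 counsellors and ICC 0.01/0.02/0.05 give:
- ρ = 0.5 (factor 0.866): power 88%/86%/80.5%
- ρ = 0.4 (factor 0.917): power 85%/82%/76%

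So the lower power in the table is not necessarily what the planned analysis would have. Baseline adjustment does not repair the type I error column, because that depends only on R.

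**The case against.** The strongest case against has four parts.

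**Unstated facts.** The document gives neither the number of counsellors nor the ICC, and it does not say that each patient keeps one counsellor. Reference to a single counsellor across calls does not settle this. If patients are shared, the design-effect formula and a simple counsellor term describe the data less well. This stands. It makes the size an assumption and the effect conditional.

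**Time point.** The primary outcome is at 12 months, calls are short, all counsellors are trained by the same team, and the second six months have no counselling beyond the call that follows the six-month assessment. The walking-pace and sitting prompts also have common triggers. Fading is plausible, and this stands as a reason to expect smaller effects. It does not remove the concern, because the goals and action plans agreed with the counsellor still feed messages up to month 12. (The Statistical analysis section places the primary outcome at six months, against 12 months elsewhere. That is a separate inconsistency, but at six months counsellor effects would be fresher.)

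**Power.** A reader might infer that the trial is underpowered. The document does not support that: uncredited baseline adjustment could more than offset the loss at small ICCs, as Step 3 shows.

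**Level of detail.** Degrees of freedom and sensitivity analyses are commonly left to an analysis plan, which is not shown here. That is fair for those details. The article does, however, state the clustering term of the primary model, and it is GP alone.

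**Conclusion.** The point holds in conditional form. The stated primary model omits a source of clustering that exists in one arm only, and any positive within-counsellor correlation at 12 months makes its standard error too small. With 10 counsellors and ICC 0.01 to 0.05, the true SE is about 3% to 15% larger and type I error about 5.8% to 9.0%. With 20 counsellors and ICC 0.01, type I error is about 5.4%; with five counsellors it could reach 13% at ICC 0.05. All of these rest on assumed counsellor numbers and ICCs and on one counsellor per patient.

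Two stronger readings go beyond the document: that the standard error is known, or shown to be likely, to be too small, and that power falls below 80%. The first would need an ICC that is not given; the second ignores the baseline adjustment that the analysis will make.

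**What to change.** - Record the counsellor's identity for each intervention patient and call. Counsellors' notes are already a data source for the process evaluation, so this should be recoverable.
- Fit the primary model with a counsellor random effect in the intervention arm only, treating each control patient as a singleton, with small-sample degrees of freedom, next to the GP effect.
- If patients are shared among counsellors, assign each to the main counsellor or present this model as a pre-specified sensitivity analysis of the primary result. If counsellors are very few, the sensitivity analysis is also a reasonable form.
- Report the number of counsellors, their caseloads and the estimated ICC.
- State in the sample-size text that 143 per arm assumes no counsellor clustering.

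The cost is analysis wording and one recorded identifier. The interval becomes slightly wider, and with about ten counsellors the counsellor variance will be imprecisely estimated. Design, recruitment and visits do not change.

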### Patient recruitment and consent

To achieve the target of 340 recruited patients, each of the 21 general practices has been asked to recruit at least 17 patients. To compensate for potential under-recruitment at individual practices, we will allow those practices that reach this target to continue recruiting until 24 patients.

Previous studies of PA interventions in primary care identified a selection bias when GPs preferentially pick those patients whom they believed to be able to use (e.g., highly educated patients) and to benefit from the intervention (e.g., patients with overweight and obesity) [29, 63]. To minimise the selection bias, we first compiled a list of all prediabetes and type 2 diabetes patients for each general practice based on their computerised medical records. At the start of the recruitment, each general practice was provided with a random selection of 24 patients from their list, i.e., 504 patients in total for all 21 practices, stratified by sex (female:male in 1:1 ratio) and condition (prediabetes:diabetes in 1:2 ratio). GPs were instructed to evaluate the eligibility criteria and introduce the study opportunistically to all eligible patients from this selection whenever they appear in the general practice for a routine health check-up [64]. For patients who are excluded or refuse to participate, GPs record the reasons. When a GP expends all the patients from this selection, they will be offered a new random selection of 12 patients from their original list. This procedure can be repeated until the respective practice exhausts its original list or reaches 24 recruited patients.

When introducing the study, GPs will mention that all enrolled patients receive a Fitbit activity tracker that they can retain after completion of the study, irrespective of the trial arm allocation. Those who agree to participate will be asked to sign a written informed consent, including consent for later access to GP records to assess long-term health outcomes. The patients will also consent for the researchers to access their PA data on their Fitbit account in line with the legal requirements.

To minimise the effect of seasonal variability on PA findings, we will attempt to spread patient recruitment evenly across 12 consecutive months. For example, GPs will be only provided with two Actigraph devices necessary for a week-long baseline assessment, so a GP cannot recruit more than four patients per month.

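### Season is named as a nuisance but left out of the outcome model, which costs a little precision in the 3- and 6-month step effects

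*Protocol article*

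**What the plan says.** The section on patient recruitment and consent gives a design measure against season. It opens "To minimise the effect of seasonal variability on PA findings" and goes on to say that the team will try to spread entry evenly over 12 consecutive months. Each practice gets two accelerometers, which caps it at four patients a month. The Trial design section expects recruitment to run from April 2022 to December 2023.

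Under Outcome measures, "Outcomes will be assessed at baseline and 3, 6, and 12 months after randomisation". Only the 12-month step change is primary there; all other outcomes and comparisons are secondary.

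The Statistical analysis section fixes a linear mixed model with practice as a random effect, "adjusted for baseline value, prediabetes/diabetes condition, and sex (fixed effects". Secondary outcomes use the same approach and are reported as a mean with a 95% confidence interval, without p-values. A further covariate enters if the arms differ meaningfully on it at baseline. The patient characteristics listed under Outcome measures for use as confounders do not include season or date. Weather appears only as a possible moderator in the micro-randomised analysis of text messages.

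**The concern.** Spreading recruitment stops the whole trial from being measured in one season. It does not take seasonal variation out of the comparison between arms, because patients then differ from one another in season, and that difference is part of the outcome variance. The baseline covariate cancels it only when follow-up falls in the same season. At 6 months every patient is measured in the opposite season from baseline, so for the seasonal component alone the baseline covariate works in the wrong direction.

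The imbalance rule would not reliably bring season in. It responds to a difference between arms, whereas season can be balanced and still predict the outcome.

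What is at stake is the width of the intervals at 3 and 6 months. Six months closes the counselling-supported lead-in phase, and the interval is all that will be reported there.

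**Working it through.** **The plan's own figure.** Inputs from the Sample size section: "To detect a difference of 1000 steps/day at 12 months between arms, with a power of 80"%, two-sided alpha 0.05, and "anticipating the standard deviation of 3000 steps/day". The normal formula gives 2 × (1.960 + 0.842)² × (3000/1000)² = 141.3, so 142 per arm. The t-based version gives 142.25, so 143. This matches "143 subjects per arm (286 in total) will be needed". Allowing for 15% attrition, 286/0.85 = 336.5, so 337 against the 340 planned. The sample size reproduces.

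**Assumptions for season (not in the documents).** All patients share one yearly sine wave with half-amplitude A = 300 to 1000 steps/day. Entry is uniform over the year. The total SD excluding season is σ = 3000 at each visit, and the baseline to follow-up correlation is ρ = 0.6.

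**Formulas.** Let s = A²/2 be the seasonal variance and k the lag in months.
- Variance at each visit: V = σ² + s
- Covariance of baseline and follow-up: C = ρσ² + s·cos(2πk/12)
- Residual variance without a season term: R0 = V − C²/V
- Residual variance with sine and cosine of the entry date: R1 = σ²(1 − ρ²) = 9,000,000 × 0.64 = 5,760,000

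**Worked example, A = 500, k = 6.** s = 125,000, V = 9,125,000 and C = 5,400,000 − 125,000 = 5,275,000. R0 = 9,125,000 − 5,275,000²/9,125,000 = 6,075,616. The ratio to R1 is 1.055, so the variance is inflated by 5.5%. With 143 per arm, SE = √(2R/143), which is 291.5 without the term and 283.8 with it, a fall of 2.6%.

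| A (steps/day) | Variance inflation, 3 months | 6 months | 12 months | SE at 6 months, without → with | Fall in SE |
|---|---|---|---|---|---|
| 300 | 1.1% | 2.0% | 0.1% | 286.6 → 283.8 | 1.0% |
| 500 | 2.9% | 5.5% | 0.3% | 291.5 → 283.8 | 2.6% |
| 750 | 6.6% | 12.1% | 0.8% | 300.5 → 283.8 | 5.6% |
| 1000 | 11.6% | 21.1% | 1.3% | 312.3 → 283.8 | 9.1% |

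**Why the lag matters.** With baseline slope b = C/V, the seasonal amplitude left in the residual is (1 + b)A at 6 months, √(1 + b²)·A at 3 months and (1 − b)A at 12 months. Baseline adjustment therefore helps at 12 months and works against the seasonal component at 6.

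**Sensitivity.** With A from 250 to 1000 and ρ from 0.5 to 0.7, the fall in SE is 0.3% to 7.1% at 3 months, 0.5% to 12.2% at 6 months and 0.0% to 0.9% at 12 months. If 3000 were instead the SD remaining after baseline adjustment, the 6-month variance inflation would be 1.3%, 3.5%, 7.8% and 13.7% for the four amplitudes in the table.

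**Bias check.** In simulation with 286 patients, a 21-month entry window, A = 1000, ρ = 0.7 and a true effect of 1000, the mean 6-month estimate was 995 without the season terms and 993 with them. The empirical SE fell from 291 to 259. Both models are unbiased.

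**Recruitment in bursts.** At four patients a month a practice can reach its target in 17/4 = 4.25 months. If each practice's entry fell within such a window, the share of seasonal variance left within practices would be 1 − [sin(x)/x]² with x = π × 4.25/12 = 1.113, that is 1 − (0.897/1.113)² = 0.35. The practice effect can absorb some of the rest. In a simulation of 21 practices with 14 patients each (ρ = 0.6, 6 months), confining entry in this way lowered the SE gain from 2.6% to 1.3% (A = 500), 4.3% to 3.2% (A = 750) and 8.9% to 5.3% (A = 1000). These figures carry Monte Carlo error, but the direction is clear.

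**The case against.** The strongest reply is that nothing here is an error. Baseline value, both stratification factors and a practice effect make a valid, conventional model. The effect estimate is unbiased without season, and the loss falls on secondary time points that have no formal test and are to be read with caution. The seasonal amplitude is assumed, so the gain could be negligible. An unseen analysis plan might already add the term.

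Most of this stands, and it limits the point to an inexpensive improvement. It does not remove the point: the article names season as something to control, then states a definite covariate list without it, and the date of randomisation is known for every patient before treatment.

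The argument from practice bursts also stands in part. The four-a-month cap does not force an even spread, but uneven recruitment by practice makes the season term less valuable, because the random effect then takes up some of the seasonal variation. Since recruitment is opportunistic, 4.25 months is the fastest a practice could go and not a forecast.

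A reader might also infer that the primary analysis is at risk, because the Statistical analysis section refers to "The primary outcome (change in daily step count at six months"). The documents do not support building that into this point. The Abstract, Trial design, Sample size, Outcome measures and Conclusions all place the primary outcome at 12 months. The six-month wording is a separate contradiction, to be reconciled on its own.

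**Conclusion.** The point holds as a minor matter of precision. Season is named and left out of the stated model, and the 3- and 6-month step effects carry shared seasonal variation that the randomisation date could explain.

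Its size depends on an assumed amplitude and correlation. Up to a half-amplitude of about 500 steps/day, the 6-month SE gain is at most about 4% over the correlations examined; at 1000 it is about 9% at correlation 0.6. Bursts of recruitment by practice would reduce it. Only the pattern common to all patients is removed, not individual responses to weather.

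Two stronger readings should be set aside. Omitting season does not bias the treatment effect, because patients are randomised individually. It does not materially weaken the 12-month primary analysis either, where the variance inflation is at most about 1.3% under these assumptions.

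**What to change.** Add one sentence to the Statistical analysis section: for the accelerometer outcomes at 3 and 6 months, the mixed model will also include the sine and cosine of the calendar date of randomisation (one-year period) as fixed effects. Using the same terms at 12 months is optional, for consistency; little gain should be expected there.

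The date is fixed at entry, so no post-randomisation variable is introduced. The cost is two degrees of freedom per model, with no new data and no change to recruitment, visits or sample size. The terms should be prespecified before unblinding and not left to the baseline-imbalance rule.
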